## Abstract

Supplemental Digital Content is available in the text

## Introduction

1

Functional dyspepsia (FD) is a functional gastrointestinal disorder that is characterized by one or more of the following symptoms; bothersome postprandial fullness, early satiation, epigastric pain, and epigastric burning that cannot be explained by any organic disease.^[1]^ The prevalence of FD ranges from 8% to 23% in Asia and from 10.3% to 20.4% in South Korea.^[2–4]^ In addition to the gastric symptoms, people with FD also suffer from abnormal daily activities and poor quality of life due to direct or indirect economic burden.^[5]^ Although the pathology of FD is unclear, there are several hypotheses that explain the mechanisms of disease. Specifically, abnormal gastric motility has been observed in FD patients as the previous studies.^[6,7]^

The Rome IV diagnostic criteria divide FD into two different subcategories:

1.postprandial distress syndrome (PDS), which is characterized by bothersome postprandial and/or bothersome early satiation, and2.epigastric pain syndrome (EPS), which is characterized by bothersome epigastric pain and/or bothersome epigastric burning.^[8]^

PDS is more prevalent than EPS in Asia,^[4,9]^ and is associated with abnormal gastric motility and gastric emptying.^[10]^

Patients with FD are conventionally treated with proton pump inhibitors, histamine-2 receptor antagonists, antidepressants, prokinetic agents, or antibiotics to eliminate *Helicobacter pylori* infection.^[11–14]^ Because of the limitations and complications of these medications, many FD patients tend to prefer alternative treatment options, such as herbal medicine.^[15–17]^*Naesohwajung-tang* (NHT) is one of the most frequently prescribed herbal medicine for treating FD in traditional Korean medicine. Although some studies have showed that NHT is effective in the treatment of FD,^[18,19]^ randomized controlled studies to provide clinical evidence of NHT as a treatment option for patients with FD have not yet been performed. The goal of this study is to propose a protocol of randomized, placebo-controlled trial aimed to evaluate the safety and efficacy of NHT in patients with FD.

## Methods and design

2

### Objective

2.1

This study aims to assess the safety and efficacy of NHT in patients with FD.

### Hypothesis

2.2

We hypothesize that the administration of NHT for 4 weeks will relieve the symptoms of FD.

### Design

2.3

This study is a prospective, multi-center, randomized, double-blind, and placebo-controlled trial. It will be conducted at Kyung Hee University Korean Medicine Hospital and Kyung Hee University Hospital at Gangdong, Seoul, Korea, from May 2019 to December 2020. This trial has been registered with the Clinical Research Information Service (CRIS) (KCT0003405, registered on December 24, 2018). Total 116 participants who meet the study criteria and consent to participate in trial will be randomly assigned into either NHT or placebo group with a ratio of 1:1. They will undergo 4 weeks of administration and another 4 weeks of follow-up period. The study flow chart illustrating the entire study procedure is shown in Figure 1 and Figure 2 shows the schedule of outcome measurements, following the Standard Protocol Items: Recommendations for Interventional Trials (SPIRIT) checklist (see Additional file 1).

**Figure 1 F1:**
[figure not shown]
Flow chart of the trial process. NHT = *Naesohwajung-tang*.

**Figure 2 F2:**
[figure not shown]
SPIRIT figure showing the schedule of enrollment, interventions, and assessments. DQ = *Damum* questionnaire, ECG = electrocardiography, EGG = electrogastrography, FD-QoL = functional dyspepsia-related quality of life, FRQ = food retention questionnaire, OTE = overall total effect, PIFD = pattern identification of functional dyspepsia, SDS = single dyspepsia symptom, TDS = total dyspepsia symptom, VAS = visual analogue scale.

### Ethics approval

2.4

The Research Ethics Committees at Kyung Hee University Korean Medicine Hospital (approval number is KOMCIRB-2017–08-030) and Kyung Hee University Hospital at Gangdong (No. KHNMCOH 2019-01-003-003) have approved this protocol. Before enrollment, all participants will sign a written informed consent form after fully informed of the purpose, process and risks associated with the trial by the investigators. The protocol is in accordance with the revised version of the Declaration of Helsinki and Good Clinical Practice guidelines approved by the Korea Food and Drug Administration.

### Sample size calculation

2.5

We hypothesize that oral administration of NHT is more effective than that of placebo in relieving FD symptoms. As the first randomized clinical trial of NHT in patients with FD, we referred to a previous study with a modified design using the same primary outcome.^[20]^ The previous study showed 1.4 points of improvement (μ_c_ – μ_t__=_*δ*) in the TDS scores for FD patients after 4 weeks of treatment with a traditional Chinese herb. In this study, the ratio (λ) of the experimental group to the control group will be 1:1, and the sample size was calculated at the 5% significance level (α) and 80% power (1 – β). The formula used to estimate the sample size is as follows, assuming that the standard deviations (SD = σ) of two groups are different and applying the larger variance in common (
[figure not shown]
): 

Considering the dropout rate as 20%, we calculated the necessary sample size to be 116 participants (58 in each group).

### Participants

2.6

#### Inclusion criteria

2.6.1

We will include the participants who meet the Rome IV criteria of FD in Table 1, classified into PDS and/or EPS. The criteria must be fulfilled for the last 3 months with symptom onset at least 6 months before diagnosis.^[1]^ The inclusion criteria for this trial are shown in Table 2.

**Table 1 T1:**
[figure not shown]
Rome IV criteria of functional dyspepsia.

**Table 2 T2:**
[figure not shown]
Inclusion criteria in the trial.

#### Exclusion criteria

2.6.2

Participants will be excluded if they meet the criteria listed in Table 3.

**Table 3 T3:**
[figure not shown]
Exclusion criteria in the trial.

### Recruitment

2.7

Advertisements will be placed on the notice boards at Kyung Hee University Korean Medicine Hospital and Kyung Hee University Hospital at Gangdong, or posted on the local public transportation.

### Randomization and allocation concealment

2.8

For randomization, an independent statistician who is not involved in the clinical aspects of the trial will generate 116 random numbers, using a randomization sequence generator the PROC PLAN of SAS 9.4 (SAS Institute Inc, Cary, NC). A manufacturer will package the investigational drugs identically to conceal the intervention allocation and label with numbers from 1 to 58 for each center (58 in each group and distributed equally to both centers).

Eligible 116 participants will be assigned into either NHT or placebo group with a consecutive random number, according to predetermined allocation list. The statistician will keep random number tables concealed within sealed opaque envelopes until the end of the study.

### Blinding

2.9

Participants, investigators, clinical research coordinators (CRCs), and pharmacists in each hospital will be blinded to group allocation throughout the study period. The one who will be associated with the randomization is only the statistician. The NHT and placebo granules are indistinguishable in appearance from each other by the naked eye, smell, or taste. The investigational drugs will be delivered to each hospital in a concealed manner to maintain blinding. The CRCs will enroll participants and assign randomization numbers sequentially at each center. The pharmacists will distribute the packaged NHT or placebo to the subjects according to random number.

### Unblinding in an emergency

2.10

If the investigators find any serious adverse events or suspect any unexpected serious adverse reactions, the event must be assessed and immediately reported to the principal investigator and the Institutional Review Board (IRB). The principal investigator will decide whether blinding should be revealed. The investigator must inform the statistician of participant's randomization number, and then the statistician must verify whether the drug taken by subject is a real NHT or placebo. In addition, these events will be recorded in the case report file (CRF).

### Withdrawal criteria

2.11

Participants are allowed to withdraw from the trial at any time during the study period. The investigators will identify and record the reason of withdrawal. The criteria for dropping out of the study are below:

when surgery or hospitalization treatment is necessary to participant due to accidents or other diseases.when participant requests to stop the study or withdraw consent to participate.when the principal investigator judges that an unavoidable reason to terminate the study has occurred.in case of serious violation of the study protocol by investigator or participant.in case of receiving a combination treatment with prohibited drugs or therapies related to FD during the study period.

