### Concomitant and forbidden drugs

3.2

Participants are not allowed to take drugs that may affect gastrointestinal tract during the study. If necessary, a wash-out period of at least 2 weeks is required before beginning the study. Any participant having received a treatment of Korean medicine to alleviate FD symptoms will be prohibited from participation. However, taking medication for the management of underlying chronic diseases, such as hypertension, diabetes mellitus, and hyperlipidemia, will be allowed. Participants will be instructed to report all the concomitant drugs and treatments conducted before, on every visit.

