#### Primary outcome

3.3.1

The total dyspepsia symptoms (TDS) scale is the primary outcome measurement to assess the change of dyspeptic symptoms. If the TDS scores show significant differences between two groups after the administration of NHT (week 4), NHT will be regarded as an effective treatment of FD. The TDS scale is comprised of eight items; postprandial fullness and bloating, early satiety, epigastric pain, epigastric burning, nausea, vomiting, belching, and other symptoms. Each item is based on a 4-point Likert scale, and higher scores are positively correlated with more severe dyspeptic discomforts.^[22]^ TDS will be evaluated at baseline, week 2, week 4, and week 8.

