### Safety assessment

3.4

The following clinical laboratory parameters will be examined to assess the safety of NHT treatment at screening and week 4; white blood cell, red blood cell, hemoglobin, hematocrit, mean corpuscular volume, mean corpuscular hemoglobin, mean corpuscular hemoglobin concentration, mean platelet volume, platelet, aspartate aminotransferase, alanine aminotransferase, gamma-glutamyl transpeptidase, blood urea nitrogen, creatinine, total cholesterol, triglyceride, high density lipoprotein cholesterol, low density lipoprotein cholesterol, glucose, erythrocyte sedimentation rate, and urinalysis. At screening, these laboratory tests and electrocardiography will be executed to decide whether a subject is eligible to enroll before randomization. In addition, adverse events reporting during the study period will be analyzed to verify the safety of NHT in patients with FD.

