### Statistical analysis

3.9

The efficacy of NHT will be analyzed on the full analysis set and per-protocol analysis. The last observation carried forward method will replace missing data to assess the robustness in the results. The safety of NHT will be assessed for the participants who are randomly assigned and received the investigational drugs at least once. The outcomes will be handled by an independent statistician.

Statistical analysis will be performed by using the SPSS program, version 20.0 (IBM SPSS Statistics, New York). The data will be expressed as mean ± standard deviation or as numbers with proportions. The changes after taking the investigational drugs will be compared between the experimental group and the control group. A chi-square test or Fisher's exact test will be used for discrete variables, while independent two sample *t* test for continuous variables. Those that do not satisfy normality will be analyzed by the Mann–Whitney *U* test as a nonparametric statistical test. The analysis of variance will be used for subgroup analysis of the changes in each pattern identification. The assessment of long-term therapeutic effects in a certain period from allocation to close-out will be performed on the basis of repeated measures design. The statistical relationship between subjective components of each assessment and objective EGG parameters will be analyzed with regression analysis. For safety assessment, the frequency and severity of adverse events and the changes in laboratory measurements will be compared between two groups. *P*-values <.05 will be regarded as statistically significant.

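### Receiving prohibited FD treatment is a reason to leave the study, not only to stop study drug, so week-4 TDS can be lost for a reason linked to the outcome

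*Protocol article*

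**What the plan says.** Section 2.11 (Withdrawal criteria) introduces its list with "The criteria for dropping out of the study are below". Two of the five entries matter here: "in case of receiving a combination treatment with prohibited drugs or therapies related to FD during the study period" and "in case of serious violation of the study protocol by investigator or participant". What is kept at that point is the reason: "The investigators will identify and record the reason of withdrawal". Section 3.2 draws the prohibition broadly: "Participants are not allowed to take drugs that may affect gastrointestinal tract during the study".

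On outcomes, section 3.3.1 states "TDS will be evaluated at baseline, week 2, week 4, and week 8", and efficacy is judged at week 4. Section 3.4 says that the laboratory parameters "will be examined to assess the safety of NHT treatment at screening and week 4". Section 3.9 names a full analysis set and a per-protocol analysis, and adds: "The last observation carried forward method will replace missing data to assess the robustness in the results". Section 2.5 allows for 20% dropout in a total of 116 participants.

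**The concern.** The entry on prohibited treatment is worded as leaving the study. Nothing in the article gives a separate rule for stopping the granules, or says that a participant who meets the entry is still seen at weeks 2, 4 or 8.

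The primary outcome is dyspeptic symptoms, and persistent symptoms are the obvious reason to take another FD treatment. The rule therefore tends to remove participants who are doing badly. If NHT works, more of them should come from the placebo arm. Neither a completer comparison nor a carried-forward score contains their true week-4 value, so the randomised comparison at the decision point is exposed to bias. Those who leave before week 4 also have no scheduled on-treatment laboratory result.

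This is a matter of trial conduct. An analysis plan can choose how to handle missing scores, but it cannot put back observations that the sites stopped collecting.

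**Working it through.** **What is lost, by timing (sections 2.3, 3.3.1, 3.4).**
- Other FD treatment before week 2: week-2, week-4 and week-8 TDS and the week-4 laboratory panel. LOCF carries baseline.
- Between weeks 2 and 4: week-4 and week-8 TDS and the week-4 panel. LOCF carries week 2.
- Between weeks 4 and 8: week-8 TDS only. The primary comparison is intact.

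**The plan's sample size.** Stated: δ = 1.4, α = 5%, power 80%, 1:1 allocation, 20% dropout, 58 per group. The SD stands in a formula that is not shown, so 116 cannot be reproduced independently. Solving backwards with two-sided α: n = 2(1.960 + 0.842)² × SD² / 1.4². At SD 2.39 this is 45.7, so 46; 46/0.80 = 57.5, so 58 per group and 116 in total. Any SD from 2.371 to 2.396 gives 58. The dropout allowance is 0.20 × 116 = 23.2 participants, from all causes.

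**Illustration A: the worst week-4 scorers leave, completers analysed.** Assumed: normal scores, SD 2.38, higher is worse, true difference 1.4. Dropping the top fraction q lowers an arm's mean by SD × φ(z)/(1 − q), where z cuts off the top q. The factor φ(z)/(1 − q) is 0.109, 0.195, 0.350 and 0.497 for q = 5%, 10%, 20% and 30%.
- Placebo 10%, NHT 5%: 1.4 − 2.38 × (0.195 − 0.109) = 1.19.
- Placebo 20%, NHT 10%: 1.4 − 2.38 × (0.350 − 0.195) = 1.03.
- Placebo 30%, NHT 10%: 1.4 − 2.38 × (0.497 − 0.195) = 0.68.
- Equal rates: no bias in this model.

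**Illustration B: the worst week-2 scorers leave.** Assumed: SD 2.4, week-2 to week-4 correlation ρ = 0.5 to 0.6, placebo 20%, NHT 10%, week-2 effect 0.7 when the week-4 effect is 1.4.
- Completers: the bias is −ρ × 2.4 × (0.350 − 0.195). This is −0.19 at ρ = 0.5 and −0.22 at ρ = 0.6, so a true 1.4 becomes about 1.21 or 1.18.
- LOCF: each arm's mean is its true mean, plus q times its average improvement from week 2 to week 4, plus (1 − ρ) × 2.4 × φ(z), with φ(z) = 0.280 at 20% and 0.1755 at 10%. At ρ = 0.6, if placebo improves by 1.0 point after week 2 and NHT by 1.7, the estimate is 1.4 + 0.2 × 1.0 − 0.1 × 1.7 + 0.4 × 2.4 × 0.1045 = 1.53.
- Simulation (58 per arm, 3,000 runs), over a range of assumed common improvement:

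| True difference | All data kept | Completers | LOCF |
|---|---|---|---|
| 1.4 | 1.39 to 1.41 | 1.16 to 1.22 | 1.42 to 1.56 |
| 0 | about 0.01 | −0.17 to −0.23 | +0.10 to +0.25 |

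With 20% dropped in both arms and a true 1.4, LOCF gives 1.4 + 0.2 × (1.0 − 1.7) = 1.26. With 5% (NHT) and 10% (placebo), completers give 1.27 and LOCF 1.49.

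**Power.** At SD 2.39, two-sided, power is about 80% with 46 observed per arm and about 88% with all 58. The second figure is an upper bound: it assumes full retention and no dilution by other treatment.

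**The case against.** Several stronger readings are tempting, and the article does not support them.

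- *Any protocol violation removes a participant, always through treatment failure.* Only serious violations count, by investigator or participant, and the hospitalisation entry concerns accidents or other diseases. A link to poor symptom control is plausible for prohibited FD treatment and weak for the rest. Even for prohibited treatment it is an inference.
- *Everyone who takes another FD treatment loses the primary endpoint.* Those who start after week 4 already have week-4 TDS and laboratory results.
- *The whole safety comparison becomes one of completers.* Section 3.9 assesses safety in everyone randomised who took at least one dose, and section 3.6 documents adverse events at each visit. Only the laboratory comparison is reduced to those who reach week 4.
- *No analysis could recover the loss.* In illustration B dropout depends only on the observed week-2 score. Regression on baseline and week 2 within arm returned 1.40, and 0.01 under no effect. The bias there comes partly from the analysis method. The article names t tests and LOCF, so the concern stays, but in narrower form.
- *LOCF would produce false-positive findings.* With no true effect and 10%/20% dropped, LOCF rejected in about 3.6% of runs despite its shift. Completers rejected in about 9%, and their shift was against NHT.
- *The 23 or so planned dropouts are treatment failures.* The 20% covers all causes.

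The best remaining defence is that a journal article condenses, and the full protocol may provide visits after withdrawal. That is possible, and it is why the loss is read from the rule as written and not asserted as fact. But the article does more than omit a detail: it states the rule as dropping out of the study and says that the reason is recorded.

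**Conclusion.** The point holds in limited form. As written, prohibited FD treatment, and likewise a serious violation, ends study participation, and no later assessment is described. For prohibited treatment before week 4, the week-4 TDS is lost for a reason plausibly linked to that outcome, and LOCF does not recover it.

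With 10%/20% dropped on week-2 scores, the completer estimate falls by roughly 0.2 points. LOCF moves by about 0.02 to 0.25 points in the other direction. With equal 20% rates and a true effect, LOCF instead falls by 0.14. If dropout follows the week-4 score itself, the completer loss is larger: 0.37 at 10%/20%. The SD, correlations, course of improvement and drop rates are all assumed, so these figures show direction and order of size and do not predict the trial's bias. The point should be acted on as a cheap improvement; it is not an error in the sample size.

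**What to change.** Leave the rules on stopping study drug unchanged. In section 2.11, separate stopping study drug from withdrawal from the study. State that, unless consent is withdrawn, participants who meet the prohibited-treatment or serious-violation entry remain for the scheduled TDS, OTE, adverse-event and week-4 laboratory assessments. Record the other treatment and its start date. Include the observed values in the full analysis set as randomised, and exclude these participants only from the per-protocol set.

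The cost is a small amendment and one CRF field, since the assessments are already scheduled. The drawback is some dilution of the week-4 contrast by the other treatment. The article does not settle the estimand: using values observed after other treatment is a choice that the sponsor should state openly. Nor does it provide for completing TDS by telephone; the calls in section 3.5 are for schedule and medication reminders.

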## Intervention

3

### Trial drugs

3.1

#### NHT

3.1.1

NHT has been frequently used as herbal medicine to alleviate dyspeptic symptoms for a long time. It is a combined prescription of *Daehwajung-eum* and *Naeso-san,* which were both described as therapies for dyspepsia in *Bangyakhappyeon*, a representative textbook of traditional Korean medicine.^[21]^ For this study, brown and bitter granules of NHT herbal extract are produced at Shinhwa Pharmaceutical Corp. (Daegu, Republic of Korea) in compliance with the Korean Good Manufacturing Practice (KGMP) guidelines.

Approximately 5.0 g of solid extract can be produced after boiling and filtering 26.73 g of herb mixture. After mixing cornstarch (0.6 g), powdered cellulose (1.4 g), and moderate amounts of purified water to the extract and then dried in granule form, we can obtain NHT granules (7.0 g), consisting of the following 19 herbs in Table 4. The NHT group will take NHT granules three times a day at 30 min after each meal for 4 weeks.

**Table 4 T4:**
[figure not shown]
Herbal plants contained in *Naesohwajung-tang.*

#### Placebo

3.1.2

The placebo granules are produced in the same facility as NHT granules, using the standard methods of placebo manufacturing based on the KGMP guidelines. The placebo granules are indistinguishable from the real NHT granules in taste, shape, weight, color, and flavor so that participants will not recognize whether they are administered for the treatment group or the control. However, the placebo does not have any components effective for treating FD. The placebo granules (7.0 g) consists of the following components; lactose hydrate (3.268 g), cornstarch (3.080 g), AF cacao color 280 (0.249 g), Sepia color powder (0.300 g), Food Red No. 40 (0.005 g), *Ssangwha* herbal flavor (0.098 g), and moderate amounts of purified water. In addition, the placebo is packaged into small sachets and labeled same as the real NHT with opaque aluminum bags. The control group will receive placebo three times a day at 30 min after each meal for 4 weeks.

Participants of each group will receive the investigational drugs at visit 1 (week 0) and visit 2 (week 2). In order to evaluate the suitability of packaging and storage conditions, and the physicochemical and biological stability of drugs during the study period, several quality assurance tests and stability tests including heavy metal analysis and microbial testing will be conducted.

